### Analysis

#### Quantitative

Primary outcome: alignment with policy recommendation will be analysed with pairwise comparisons (intervention group 1 vs control, intervention group 2 vs control, and intervention group 1 vs intervention group 2) performed using the sign rank test for ordinal data among matched pairs. This primary analysis will be conducted at both the cluster level and ward level. Analysis will be undertaken according to ‘as randomised’ (intention-to-treat) principles. Where it is identified that participants have moved between clusters allocated to different intervention groups during the study period, we will undertake a contamination-adjusted intention-to-treat analysis.

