### Eligibility criteria

Allied health managers responsible for weekend allied health resource allocation decisions will be eligible for inclusion. All allied health professions currently providing an inpatient service to acute general medical and surgical wards, and sub-acute rehabilitation wards are eligible. A representation of the different allied health professions (e.g. physiotherapy, occupational therapy, speech pathology, dietetics, podiatry, psychology, exercise physiology, and social work) will be sought. We shall include those who currently provide weekend allied health services as well as those who do not currently provide services, but could potentially introduce these services.

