### Outcomes

#### Primary outcome: alignment of weekend allied health service provision with policy recommendations at 12-month follow-up

Allied health service events (occasions of service) occurring during weekends, as a proportion of total allied health service events for the relevant hospital wards over a 1 month period will be used to determine alignment with the policy recommendation. This information will be collected at baseline for the preceding calendar month and the same corresponding calendar month at the 12-month follow-up. Allied health service events will be defined as per the 2017 National Allied Health Data Working Group (NAHDWG) endorsed National Allied Health Best Practice Data Sets (Additional file 1). Where data relating to allied health service events during weekends and weekdays is not available, data relating to allied health staffing levels or budgetary allocations during the weekend as a proportion of total allied health staffing levels or budgetary allocations for the relevant wards at each hospital for the preceding month will be used. Each participant cluster (hospital/health service) will receive a single classification as either (1) practice fully aligned with policy recommendation for both acute and sub-acute hospital wards, (2) practice partially aligned with policy recommendations (e.g. if practice on acute wards is completely aligned with the policy recommendation but not on sub-acute wards, and vice versa), or (3) practice not aligned with policy recommendation.

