### Sample size

The sample size estimate was calculated based on the units of assessment of the primary outcome ‘alignment of weekend allied health service provision with policy recommendations at 12-month follow-up’. The most conservative unit of assessment for this outcome will be clustered at individual hospitals/health services with geographically distinct decision makers. We therefore conducted our power analysis at this “cluster-level” rather than at the ward-level or individual decision-maker level (as one hospital/health service may have multiple decision makers involved). A sample size of 25 clusters (hospitals/health services) per group will provide greater than 80% power under the assumption that 50% of participants in an intervention group and 10% in the control group will completely align with the policy recommendation. We will aim to recruit 27 clusters (hospitals/health services) per group to allow for approximately 5–10% loss to follow-up in each group. Assumptions regarding statistical power and expected loss to follow-up were derived from a similar randomised controlled trial by Dobbins et al. [33]. Based on data from a survey of physiotherapy services provided outside business hours in Australian hospitals by Shaw et al. [41], and allied health staffing levels for health service inpatients in Victoria [56], it is anticipated that none of the recruited health services will be completely aligned with the evidence-based policy recommendation at baseline. This analysis was performed using Stata 13 (StataCorp, 2013. Stata Statistical Software: Release 13. College Station; TX: StataCorp LP).

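### The primary test makes no use of the baseline weekend-service data that every cluster supplies, so it may forgo precision and leaves the result exposed to chance baseline imbalance

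*Protocol article*

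**What the plan says.** The primary outcome section defines the measure as weekend service events over all service events in one month and states: "This information will be collected at baseline for the preceding calendar month and the same corresponding calendar month at the 12-month follow-up". From this share each cluster is placed in one of three classes: fully, partially or not aligned. Partial can mean that acute wards meet the recommendation and sub-acute wards do not, or the reverse. The section heading sets the outcome at 12-month follow-up.

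The quantitative analysis section reads "Primary outcome: alignment with policy recommendation will be analysed with pairwise comparisons" (each intervention against control, and the two interventions against each other), using a signed-rank test for ordinal data in matched pairs. It names no baseline value and no covariate. The trial design section bases matching on regional status, and the randomisation is stratified on the same factor only.

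Two statements bear on how clusters will look at entry. The eligibility section includes "those who currently provide weekend allied health services as well as those who do not currently provide services". The sample size section says "it is anticipated that none of the recruited health services will be completely aligned with the evidence-based policy recommendation at baseline". It is silent on how many will be partially aligned.

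**The concern.** The outcome is a service pattern that each site already has in some form when it joins. A site that starts with one ward type aligned has less to change than a site with neither, so baseline status plausibly predicts the 12-month class. If it does, a comparison of follow-up classes alone carries between-site variation that the trial has already measured. With about 25 clusters per arm, the arms can also differ at entry by chance. Randomisation is stratified on region but not on baseline alignment, and the named test has no means of correcting for such a difference. At stake are some precision and the credibility of the realised result if the arms turn out uneven. The validity of the test is not at stake.

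**Working it through.** **1. The plan's own figure.** The sample size section says "A sample size of 25 clusters (hospitals/health services) per group will provide greater than 80% power", assuming "50% of participants in an intervention group and 10% in the control group will completely align with the policy recommendation". Alpha is not stated; I take 0.05 two-sided.

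- Uncorrected: n = [1.96·√(2·0.3·0.7) + 0.842·√(0.5·0.5 + 0.1·0.9)]² / 0.4² = 19.4, so 20 per group.
- Continuity-corrected: (n/4)·[1 + √(1 + 4/(n·0.4))]² with n = 20 gives 24.7, so 25 per group. This matches the protocol.
- Power at 25 per group: 89.5% uncorrected, 83.3% by Fisher's exact test, 81.8% continuity-corrected.

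The stated power is therefore reached on the protocol's two-proportion calculation without any baseline adjustment.

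**2. What can vary at baseline.** Under the protocol's expectation, full alignment at baseline is 0% in every group. That indicator is constant, and adjusting for it gains nothing. What can vary is partial versus none, and the underlying weekend share. The document gives neither distribution, nor their relation to outcome.

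**3. Effect on the three-level scale, 40% partial at baseline (assumed).** Setup: 25 clusters per arm, full alignment at 12 months 50% versus 10% or close to it. An unpaired rank-sum test is compared with a van Elteren test stratified on baseline class. The unpaired test stands in for the planned one because the protocol does not say how pairs are formed. Each row collects runs with different assumed transition probabilities.

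| Link between baseline class and outcome | Power, unadjusted → stratified |
|---|---|
| None | 86% → 85%; 83% → 82% |
| Modest | 81% → 83%; 78% → 81%; 83% → 87%; 80% → 86% |
| Strong | 83% → 98%; 79% → 94%; 80% → 96%; 74% → 93% |

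The changes are about -1 point, +2 to +6 points, and +15 to +19 points.

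**4. Sensitivity to the partial share.** In one fully specified model, a site not fully aligned at 12 months is partial with probability 0.9 if it was partial at baseline and 0.1 if it was not. Its chance of full alignment is p + d·(1-q)·2p(1-p) if partial at baseline and p - d·q·2p(1-p) if not. Here p = 0.1 or 0.5 by arm, q is the share partial at baseline, and d is the dependence of full alignment on baseline. There were 2,000 runs per cell.

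| q | d = 0 | d = 0.5 | d = 0.9 |
|---|---|---|---|
| 0 | no change | no change | no change |
| 10% | 81% → 84% | 82% → 85% | 76% → 83% |
| 30% | 78% → 84% | 72% → 85% | 65% → 87% |
| 50% | 78% → 84% | 66% → 84% | 60% → 88% |

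Even the d = 0 column assumes that partial status strongly persists, so this grid leans towards a gain. With 10% partial and a modest link, another assumed model gave no change (83% both ways).

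**5. Chance imbalance.** Let X and Y be independent Binomial(25, 0.4) counts of partially aligned clusters in two arms. A 20-point difference is 5 clusters, and P(|X - Y| ≥ 5) = 19%. The chance that at least one of the three pairs of arms differs by that much is about 39-40%. With strong dependence and no true effect, the unadjusted test rejects in about 17-19% of the trials that are imbalanced in this way, against about 5% for the stratified test. Over all trials both tests reject near 5%.

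**The case against.** The strongest reply is that this is a question of efficiency and not an error. An unadjusted comparison of randomised clusters is valid, its error rate already allows for chance imbalance, and the planned power is reached without adjustment. All of that stands.

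A reader might also infer that sites will certainly start at different levels and that the trial is throwing away power. The documents do not support this. The protocol expects every site to share the same status on full alignment, the criterion behind the sample size. Having a weekend service is also not the same as being partially aligned. The 40% share and every dependence used above are assumptions, and if no site starts partially aligned, adjusting for class gains nothing. Nor are the simulated figures the power of the planned test, which is paired.

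Two further replies carry less weight. One is that the signed-rank test might use baseline, since the abstract mentions the measure at both time points. But the comparisons are group against group and the stated matching is on region, so the pairs do not appear to be baseline-to-follow-up pairs. The other is that adjustment belongs in a separate analysis plan. That is often so, but here the protocol itself fixes the primary test, and as worded the test leaves no place for baseline.

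The constancy of full alignment at baseline does not settle the matter either. The planned analysis ranks three classes, and partial versus none can still predict who reaches full alignment.

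**Conclusion.** The point holds as a low-cost improvement. Baseline data on the outcome variable are collected, sites are likely to differ at entry in weekend share and possibly in partial versus no alignment, and the primary test uses none of this. The likely benefit ranges from nothing (or a loss of 1 point of power) with no dependence, through about 2 to 6 points with modest dependence, to about 15 points or more with strong dependence. These figures assume 25 clusters per arm, 40% partial at baseline and unpaired rank tests. Adjustment would also protect the reading of the result if the arms were uneven at entry. It is neither a bias nor a demonstrated loss of power: type I error stays near 5% with or without adjustment, and the protocol's own calculation reproduces.

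**What to change.** Prespecify the primary between-group comparison, before the data are analysed, as one of the following:

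- a proportional-odds model for the three-level class at 12 months, with baseline class (not versus partial, since full is expected to be empty) and the metropolitan/regional randomisation stratum as covariates; or
- a van Elteren test stratified on baseline class.

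State in advance how strata are collapsed if cells are sparse, which is a real prospect with about 25 clusters per arm.

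An ANCOVA of 12-month distance from the recommended weekend share on baseline distance is an optional supportive analysis. It is usable only where a comparable numeric share exists at both time points, because the protocol allows staffing or budget figures in place of event counts and classifies acute and sub-acute wards jointly.

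The cost is a change of analysis wording and a rule for sparse strata. No further data collection is needed.

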## Methods

### Trial design

This multi-centre study will be evaluated using a three-group matched (based on health service regional status) parallel cluster randomised controlled trial. A three-group design will allow the comparison of two different research implementation strategies with a control. Stratification will be based on self-reported health service geographical classification as metropolitan or regional (including rural and remote), and clustering will occur at the level of weekend allied health resource allocation decision-making within each health service (e.g. health service level or hospital level).

This evaluation will be based on the Kirkpatrick Evaluation Model Hierarchy framework, which has four outcome levels that are designed as a sequence of ways to evaluate training programs [44, 45]. This study will focus on behaviour change outcomes in the third category.

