### Assignment and concealment of implementation strategy group allocation

Study investigators will consult with health service representatives to determine decision-making structure for weekend allied health services within their health network. Some health services in Australia are comprised of multiple geographically separated hospitals that report to the same board but have independent decision-making processes in relation to weekend allied health service provision decisions. They will be treated as separate units of recruitment and randomisation, where health service representatives report that decision-making for geographically distinct hospitals is independent and that they anticipate ability to prevent contamination of the intervention between sites within their network. Units of randomisation (hospitals or health services) will then be stratified according to geographic location. A random number sequence will be generated using an online software application (Sealed Envelope Ltd. 2018. Create a blocked randomisation list. [Online] Available from: https://www.sealedenvelope.com/simple-randomiser/v1/lists), incorporating permuted blocks of randomly selected sizes of three, six, or nine, and stratified according to metropolitan or regional status. This random number sequence will be generated and held by a single investigator ([name]) in a secure location so that investigators conducting recruitment and data collection are blinded to the allocation status of participating sites and the allocation of the next site to be recruited.

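### The primary signed-rank test is run at ward level as well as cluster level, both called primary, with no stated allowance for clustering of wards within the randomised hospital or health service

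*Protocol article*

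**What the plan says.** **Unit of randomisation.** Under Trial design, "clustering will occur at the level of weekend allied health resource allocation decision-making within each health service". Under Assignment and concealment, the randomised units are named again: "Units of randomisation (hospitals or health services) will then be stratified according to geographic location". Wards are not randomised.

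**Outcome.** The Primary outcome section defines a three-level scale (fully, partially or not aligned) and assigns it per cluster: "Each participant cluster (hospital/health service) will receive a single classification". The example given for the middle category is one ward type meeting the recommendation while the other does not.

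**Sample size.** "The most conservative unit of assessment for this outcome will be clustered at individual hospitals/health services with geographically distinct decision makers". The power calculation was therefore done at cluster level, "rather than at the ward-level or individual decision-maker level (as one hospital/health service may have multiple decision makers involved".

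**Analysis.** The three pairwise comparisons are to be "performed using the sign rank test for ordinal data among matched pairs". Then: "This primary analysis will be conducted at both the cluster level and ward level". Neither level is given precedence, and no clustered form of the test, model or robust variance is named.

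**Economic evaluation.** The cost-effectiveness ratio counts additional clusters and additional wards that reach complete alignment, so a ward is there treated as either completely aligned or not.

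**The concern.** The signed-rank test assumes independent pairs. Wards in one hospital or health service share the allocation, the document, any knowledge-broker contact and the decision-making unit. The decision being targeted (Objectives) is how weekend resources are divided between acute and sub-acute wards, so one decision can move several wards at once. Correlation between wards of a cluster is the expected case, and a test that counts each ward pair as a separate observation understates the variance.

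Both levels carry the label primary. If the cluster-level result were null and the ward-level result significant, the Analysis text would allow the ward-level p-value to be reported as a primary finding, although it comes from the less conservative of the two units.

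**Working it through.** **1. Reproduce the plan's own figure.** Inputs from Sample size: 50% versus 10% complete alignment, 25 clusters per group, power above 80%. Alpha is not stated there; two-sided 0.05 is assumed.

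- Uncorrected: n = [1.960·√(2·0.3·0.7) + 0.842·√(0.5·0.5 + 0.1·0.9)]² / 0.4² = (1.270 + 0.491)² / 0.16 ≈ 19.4, so 20 per group.
- With continuity correction: 25 per group, the stated figure.
- Power at 25 per group: 89.5% (normal approximation) or 83.3% (Fisher's exact test). Both exceed 80%.

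The stated 25 is therefore a cluster-level number and is not in dispute.

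**2. Effect of pooling wards.** With a yes/no outcome per ward, the signed-rank statistic depends on the difference between arms in the number of aligned wards. With m wards per cluster and correlation ICC between them, the variance of that difference is multiplied by

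DE = 1 + (m − 1)·ICC.

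A test that ignores this has actual two-sided error

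α* = 2·[1 − Φ(1.96/√DE)].

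Example, m = 2 and ICC = 0.3: DE = 1.3, 1.96/√1.3 = 1.72, α* = 8.6%. Example, m = 4 and ICC = 0.5: DE = 2.5, 1.96/√2.5 = 1.24, α* = 21.5%.

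**3. Range.** Neither m nor ICC is in the article, so both are assumed. The formula was checked by simulating the signed-rank test on 25 cluster pairs with m ward pairs each, beta-binomial ward outcomes and no true effect (8,000 runs per setting), with 10% or 30% of wards aligned in both arms.

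| Wards per cluster | ICC | DE | α* (formula) | Simulated, 10% aligned | Simulated, 30% aligned |
|---|---|---|---|---|---|
| 2 | 0.1 | 1.1 | 6.2% | 5.2% | 6.8% |
| 2 | 0.3 | 1.3 | 8.6% | 7.3% | 8.5% |
| 2 | 0.5 | 1.5 | 11.0% | 10.0% | 11.1% |
| 4 | 0.1 | 1.3 | 8.6% | 8.1% | 8.9% |
| 4 | 0.3 | 1.9 | 15.5% | 15.7% | 15.8% |
| 4 | 0.5 | 2.5 | 21.5% | 21.6% | 22.2% |
| 6 | 0.1 | 1.5 | 11.0% | 10.4% | 10.5% |
| 6 | 0.3 | 2.5 | 21.5% | 22.2% | 20.4% |
| 6 | 0.5 | 3.5 | 29.5% | 30.7% | 29.2% |

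With ICC = 0 the simulated ward-level error was 4.4% to 5.4%, so the excess comes from the correlation alone.

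**4. Cluster level.** In the same simulations, the signed-rank test on one three-level value per cluster rejected in 3.6% to 5.1% of runs over all settings.

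**The case against.** The strongest reply is that one sentence in a condensed article names a test family and does not say that clustering will be ignored. Clustered signed-rank tests exist, and an analysis plan could specify one. Ward level could also mean acute and sub-acute wards analysed separately with one status per cluster, in which case there is no replication within a cluster and no inflation. Both routes would remove the problem, but neither is in the text. The text takes one named test and applies it at ward level as a primary analysis; that is a stated rule, not a detail left open.

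Other parts of the reply stand and limit the point. A reader might infer any of the following, and the article does not support them:

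- **That no valid ward-level outcome exists.** The middle category is illustrated by a contrast between ward types, which a single ward cannot show. But the Economic evaluation section implies a yes/no status per ward, and a signed-rank test can be run on two levels. What is missing at ward level is only an explicit scale.
- **That nothing indicates which level matters.** The outcome definition and the power calculation both point to the cluster. The defect is that the Analysis section extends the label primary to wards without ranking the two.
- **That wards in a hospital share one decision-maker.** Sample size allows for several. They share a decision-making unit, which is enough to expect positive correlation.
- **That reported intervals would be too narrow.** The Quantitative section plans tests and mentions no intervals.
- **That the inflation is known to be large.** Its size rests entirely on assumed ward counts and ICCs.

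**Conclusion.** The point holds in limited form. As written, the ward-level primary analysis has no stated allowance for clustering on the randomised unit. If wards are pooled as independent pairs, its false-positive rate exceeds 5% for any positive ICC with more than one ward per cluster. Under assumed ICCs of 0.1 to 0.5 it is about 6-11% with two wards per cluster, 9-22% with four and 11-30% with six. With two wards and an ICC of 0.1 or less the excess is negligible (simulated 5.2% and 6.8% at ICC 0.1). The direction is firm; the size is conditional on figures that the article does not give.

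A reader might go further and conclude that the trial's main answer is invalid. It is not: the cluster-level analysis, on which the sample size rests, keeps its error rate. The risk is confined to the ward-level result and to its being presented as primary.

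**What to change.** In the Quantitative analysis section:

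1. State that the cluster-level comparison is the sole primary analysis.
2. Make the ward-level comparison secondary, with a binary outcome: ward aligned with the recommendation, yes or no.
3. Name a ward-level method that accounts for clustering on the randomised hospital or health service. A permutation test that reallocates whole clusters or a clustered rank test would do. A GEE or mixed model with a small-sample correction is an alternative if event numbers allow. At the assumed 10%, only about 0.10 × 25 = 2.5 control clusters would be completely aligned, so such a model may be unstable and should not be the only option.

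**Cost.** Wording only. No extra sites or data are needed, since Data collection already requests the ward location of each service event. The ward-level p-values will be larger than those of the unadjusted test, and correct.
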